## Abstract

**Background:**

Insomnia is a common but frequently overlooked sleep disorder after stroke, and there are limited effective therapies for insomnia following stroke. Traditional Chinese medicine (TCM), including acupuncture and the Chinese herbal medication (CHM) Suanzaoren decoction (SZRD), has been reported as an alternative option for insomnia relief after stroke in China for thousands of years. Here, this study aims to investigate the efficacy and safety of electroacupuncture (EA) in combination with SZRD in the treatment of insomnia following stroke.

**Methods:**

A total of 240 patients with post-stroke insomnia will be included and randomized into four groups: the EA group, SZRD group, EA & SZRD group, and sham group. The same acupoints (GV20, GV24, HT7, and SP6) will be used in the EA group, EA & SZRD group, and sham group, and these patients will receive the EA treatment or sham manipulation every other day for 4 consecutive weeks. SZRD treatments will be given to participants in the SZRD group and EA & SZRD group twice a day for 4 consecutive weeks. The primary outcome measures include Pittsburgh Sleep Quality Index scores and polysomnography. Secondary outcome measures include the Insomnia Severity Index, the National Institutes of Health Stroke Scale, the Hospital Anxiety and Depression Scale, brain magnetic resonance imaging, functional magnetic resonance imaging, and nocturnal melatonin concentrations. The primary and secondary outcomes will be assessed at baseline (before treatment), during the 2nd and 4th weeks of the intervention, and at the 8th and 12th weeks of follow-up. Safety assessments will be evaluated at baseline and during the 4th week of the intervention.

**Discussion:**

This study will contribute to assessing whether the combination of these two therapies is more beneficial for post-stroke insomnia than their independent use, and the results of this clinical trial will improve our understanding of the possible mechanisms underlying the effects of combination therapies.

**Trial registration:**

Chinese Clinical Trials Register ChiCTR2000031413. Registered on March 30, 2020

## Introduction

### Background and rationale {6a}

Stroke is the second leading cause of death and a major cause of disability worldwide. It has become one of the major contributors to the increased prevalence, incidence, and mortality of vascular disease [1]. Over 2 million people suffer a stroke in China every year [2]. Insomnia is the most common disorder of the sleep-wake cycle, affecting approximately 50% of stroke survivors [3]. Insomnia is defined as repeated difficulties in initiating or maintaining sleep or early awakening accompanied by daytime functional impairment [4]. In some cases, insomnia that develops in young adulthood may be a higher risk factor for stroke than insomnia that develops later [5]. On the other hand, insomnia may directly result from cerebral ischaemia or anoxia during stroke or environmental conditions in inpatient wards or stroke-related medical conditions such as pain, depression, infections, and drug-induced side effects [6, 7]. Insomnia following a stroke can deteriorate cognitive and physical function, contributing to a worse outcome during rehabilitation [8]. Currently, the American Academy of Sleep Medicine guideline recommends cognitive behaviour therapy as a treatment for insomnia, but it is not easily or widely available [9]. Meanwhile, the side effects of hypnotic medications, such as drowsiness, fatigue, and dizziness, limit their usage in patients with post-stroke insomnia [10]. Thus, owing to the lower side effects and holistic efficacy, complementary and alternative therapies, including acupuncture and/or Chinese herbal medication (CHM), have been incorporated into the treatment of insomnia following stroke worldwide [11].

Electroacupuncture (EA), a new form of acupuncture where a small electric current is passed between pairs of acupuncture needles, has shown positive effects on several biological parameters, such as enhancing cognitive function, learning, memory, and sleep following stroke [12]. EA beneficially regulates a healthy mental state by stimulating some special meridian points [13]. Based on theories in traditional Chinese medicine (TCM), the acupoints of the *Governor meridian* (Dumai in Chinese) and the *Shaoyin meridian* (Shaoyin Jing in Chinese) are the most common acupoints used for the treatment of stroke and its complications [14]. The distal acupoints are commonly matched with the local acupoints based on the mechanism of the disease in accordance with the theory of TCM. A systematic review of the effects of acupuncture on insomnia after stroke has shown potential benefits in the treatment of insomnia and for improving patients’ sleep quality [15].

Chinese medicinal herbs and formulas have also been widely used to treat some neurological diseases, such as stroke, depression, and insomnia, in China and some Asian countries for thousands of years [16]. In recent decades, some of them have also been recommended worldwide to alleviate insomnia [17]. Suanzaoren decoction (SZRD), a well-known Chinese medicinal formula for insomnia, is a combination of five CHMs based on TCM theory and includes Suanzaoren (Ziziphi Spinosae Semen), Fuling (Poria cocos), Chuanxiong (Ligusticum wallichii), Zhimu (Anemarrhenae), and Gancao (Glycyrrhiza) [18]. A previous meta-analysis showed that SZRD solely or combined with other treatments could promote sleep quality and prolong sleep duration [19].

Therefore, combining EA with SZRD into a treatment method can potentially be used in the clinical therapy of post-stroke insomnia patients.

## Objectives {7}

Although some studies have shown acupuncture combined with SZRD is more beneficial for insomnia [20, 21], whether EA combined with SZRD is more effective and safer for insomnia after stroke needs more clinical and experimental evidence. Therefore, we will combine EA with SZRD as a clinical treatment method for patients with post-stroke insomnia. We aim to assess whether the combination therapies are more effective and safer for insomnia after stroke than independent usage of the two treatments and to preliminarily uncover the possible mechanisms underlying the effect of the combination therapy.

## Trial design {8}

The study is designed as a 12-week, single-centre, randomized, single-blind, controlled trial. Study participants will be included according to the inclusion and exclusion criteria. Before starting the treatment, all eligible patients will undergo a standard neuroimaging examination (brain magnetic resonance imaging and functional magnetic resonance imaging), a baseline evaluation of sleep quality, neurological deficits, anxiety and depression, and measurement of nocturnal melatonin concentrations. Then, subjects will be equally randomized into four groups: the EA group, SZRD group, EA & SZRD group, and sham group. Patients in the EA group and sham group will receive EA stimulation or sham EA every other day for 4 consecutive weeks for a total of 14 sessions. Patients in the SZRD group will only take SZRD granules orally twice a day for 4 consecutive weeks. Patients in the EA & SZRD group will be administrated SZRD granules orally twice a day for 4 consecutive weeks, combined with EA stimulation every other day for 4 consecutive weeks, for a total of 14 sessions. Assessments will be carried out at baseline (before treatment), during the 2nd and 4th weeks of the intervention, and at the 8th and 12th weeks of follow-up.

The trial will be performed according to the principles of the Declaration of Helsinki (Fortaleza version, 2013), the Consolidated Standards of Reporting Trials [22], the Standards for Reporting Interventions in Clinical Trials of Acupuncture [23], and Recommendations for Intervention Trials (SPIRIT) Checklist.

## Methods: participants, interventions, and outcomes

### Study setting {9}

A total of 240 patients with post-stroke insomnia will be recruited through advertisements on the WeChat official platform and hospital bulletin boards at the College of Traditional Chinese Medicine, China Three Gorges University & Yichang Hospital of Traditional Chinese Medicine. Written informed consent will be provided by all patients at the time of recruitment. Patients will have an equal chance of being randomly allocated to the EA group, SZRD group, EA & SZRD group, and sham group. Due to the limitations of the intervention methods, the therapists will not be blinded. The assessors will perform the evaluations and analysis of the outcomes at five points (before treatment, during the 2nd and 4th weeks of the intervention, and the 8th and 12th weeks of follow-up). Data management and statistics will be conducted at the Medical College of China Three Gorges University. The flow chart is shown in the SPIRIT Figure (Fig. 1).

**Fig. 1 Fig1:**
[figure not shown]
Flow chart. EA, electroacupuncture; SZRD, Suanzaoren decoction; PSQI, Pittsburgh Sleep Quality Index; PSG, polysomnography; ISI, Insomnia Severity Index; NIHSS, National Institutes of Health Stroke Scale; HADS, Hospital Anxiety and Depression Scale; MRI, brain magnetic resonance imaging; fMRI, functional magnetic resonance imaging; MLT, nocturnal concentration of melatonin

### Eligibility criteria {10}

#### Inclusion criteria

Participants who meet the following criteria will be included in the trial:
Aged 18–70 years, either sex;Fulfilling the diagnostic criteria of stroke based on the Chinese guidelines for diagnosis and treatment of acute ischemic stroke 2018 [24] or Chinese guidelines for diagnosis and treatment of acute intracerebral haemorrhage 2019 [25];After acute stroke; andFulfilling the diagnostic criteria of insomnia according to the *Diagnostic and Statistical Manual of Mental Disorders, fifth edition* [4].

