#### Exclusion criteria

Participants who meet the following criteria will be excluded from the trial:
Had insomnia before stroke;Insomnia by poor sleep conditions [26];Have diagnoses of other sleep disorders, such as narcolepsy, obstructive sleep apnoea syndrome, or restless legs syndrome;Have neurological or psychiatric diseases;Have severe diabetes; hypertension; severe liver, kidney, or thyroid dysfunction; and severe cardiac insufficiency;Are unable to read, understand, and complete the forms or use the rating scales;Have implants that could interfere with EA or a history of hypersensitivity to EA;Had received TCM in the previous 1 month;Had participated in other trials;Are taking sleep-affecting diet or medication; orAre pregnant or preparing for pregnancy.

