## Assignment of interventions: allocation

### Sequence generation {16a}

The investigator at Yichang Hospital of Traditional Chinese Medicine will generate random numbers 001–240 by SPSS 20.0 software (SPSS Inc., Chicago, IL, USA) and places random numbers in a sequenced, sealed, opaque envelope.

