### Concealment mechanism {16b}

The random numbers in the sequenced sealed opaque envelopes will have been equally allocated to the four groups (0, 1, 2, or 3 group). The principal investigator, who will enrol the eligible patients, will open the envelopes based on patients’ registration order numbers and then assign the patients to groups 0, 1, 2, or 3 in accordance with the group number in the envelope. The random numbers will be placed in opaque sealed envelopes to prevent selection bias. The researchers, data collection staff, and data analysts will be blinded in the course of the random allocation sequence to avoid detection bias.

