### Methods for additional analyses (e.g. subgroup analyses) {20b}

Multivariate logistic regression will be used to conduct exploratory analyses. Based on insomnia duration, insomnia can be categorized into acute insomnia (lasting up to three months) and chronic insomnia (lasting at least 3 months) [39]. A subgroup analysis will be conducted based on the duration of insomnia after stroke.

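### Insomnia duration is singled out for a subgroup but used in neither the allocation nor the stated main analysis, which leaves modest, avoidable noise in the combination-versus-single-therapy contrasts

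*Protocol article*

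**What the plan says.** All references are to the protocol article.

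- **Entry.** Under Inclusion criteria the only timing condition is "After acute stroke; andFulfilling the diagnostic criteria of insomnia". Under Exclusion criteria the only limit on when the insomnia began is "Had insomnia before stroke". No minimum or maximum is written for time since stroke or for insomnia duration.
- **Duration as a factor.** Methods for additional analyses {20b} divides patients into "acute insomnia (lasting up to three months) and chronic insomnia (lasting at least 3 months" and commits to its use: "A subgroup analysis will be conducted based on the duration of insomnia after stroke". A patient at exactly three months falls into both categories.
- **Allocation.** Under Sequence generation {16a} the investigator "will generate random numbers 001–240 by SPSS 20.0 software". Under Concealment mechanism {16b} the numbers are divided equally over four groups, and the principal investigator "will open the envelopes based on patients’ registration order numbers". No stratum is described.
- **Analysis.** Statistical methods {20a} describes repeated measures comparisons with Bonferroni correction. It names neither insomnia duration nor time since stroke.
- **Natural course.** Background and rationale {6a} attributes part of post-stroke insomnia to "environmental conditions in inpatient wards or stroke-related medical conditions such as pain, depression, infections, and drug-induced side effects". Some of these causes can resolve without treatment.

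**The concern.** The protocol treats insomnia duration as important enough to define two categories and plan a subgroup, so its authors expect both kinds of patient. Patients soon after stroke, or with recent insomnia, may improve over the 12 weeks in any arm, on PSQI and on NIHSS. If so, duration explains part of the outcome variance. A design that neither balances the factor nor adjusts for it leaves that variance in the error term.

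This matters most where effects are likely to be small. The Objectives section asks whether the combination beats each therapy used alone. The sample size section rests on a 3.97-point gap between an intervention and a control group in an earlier study, and the article gives no expected size for combination against single therapy. Such a contrast may well be smaller, and then precision counts.

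**Working it through.** **Inputs from the article.** PSQI at 4 weeks 9.21 (SD 4.05) and 13.18 (SD 4.32), two-sided α 0.05, power 0.90, 25 per group needed, 60 per group recruited (Sample size {14}).

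**Assumptions, because the article gives no figures.** Acute share p = 0.5, with 0.3 as a check. Acute-minus-chronic difference in spontaneous PSQI recovery g = 1 to 3 points. True between-arm difference of 2 points for combination against single therapy. All 60 per arm analysed, α 0.05 without Bonferroni.

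**1. The plan's own figure.** δ = 13.18 − 9.21 = 3.97. Pooled variance = (4.05² + 4.32²)/2 = 17.53, so SD = 4.187. With n = 2σ²(1.960 + 1.282)²/δ², the pooled SD gives 23.4, rounded up to 24. The larger SD of 4.32 gives 24.9, rounded up to 25. The stated 25 reproduces.

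**2. Precision as planned.** SE of a pairwise contrast = 4.187 × √(2/60) = 0.764. Power = Φ(δ/SE − 1.96):
- δ = 3.97: Φ(5.19 − 1.96), above 99%.
- δ = 2: Φ(2.62 − 1.96) = 74%.

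**3. Precision with the duration variance removed.** The mixture contributes p(1 − p)g². First take the stated SDs as already containing it, so that adjusted SE = √(17.53 − p(1 − p)g²) × √(2/60).

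| p | g | Mixture variance | Share of 17.53 | SE | Power for 2 points |
|---|---|---|---|---|---|
| 0.5 | 1 | 0.25 | 1.4% | 0.759 | 75% |
| 0.5 | 2 | 1.00 | 5.7% | 0.742 | 77% |
| 0.5 | 3 | 2.25 | 12.8% | 0.714 | 80% |
| 0.3 | 1 | 0.21 | 1.2% | 0.760 | 75% |
| 0.3 | 3 | 1.89 | 10.8% | 0.722 | 79% |

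If instead the mixture comes on top of the stated SDs, then at p = 0.5 the SD rises to between 4.22 (g = 1) and 4.45 (g = 3). Unadjusted power for 2 points is then 74% down to 69%, and adjustment restores about 74%. The gain is of similar size on either reading.

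**4. Chance imbalance.** The acute share of two arms of 60 differs with SE √(2 × 0.5 × 0.5/60) = 0.091, a 95% range of ±18 percentage points. Multiplied by g = 1 to 3, this shifts a contrast by up to ±0.18 to ±0.54 PSQI points. The 95% half-width of the unadjusted contrast is 1.96 × 0.764 = 1.50, and the shift is one component of that interval.

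**The case against.** The strongest case against the point is that nothing here is an error. Randomisation leaves every contrast unbiased, chance imbalance is ordinary sampling variation, and stratification is optional with 60 per arm. That is right as far as bias goes. A reader might infer from open entry and a single list that the comparison is distorted, or that the shifts in step 4 are an error additional to the confidence interval. The documents support neither inference.

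Other objections stand in part:

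- **Transient causes.** The exclusion criteria remove insomnia due to poor sleep conditions, patients on sleep-affecting diet or medication, and psychiatric disease. Much of the passing insomnia listed in the background is thus kept out. Pain and infection remain, and the article gives no recovery figure by duration, so g is purely an assumption. The cited diagnostic criteria may carry a duration rule that the article does not reproduce, but {20b} plainly expects acute cases.
- **The 2-point figure.** One might compare the shifts with the 2-point PSQI response in {20a}. That is a within-patient threshold, not a between-arm difference. The 2 points used here are a separate assumption.
- **The subgroup.** One might conclude that an unstratified list spoils the duration subgroup. Unequal counts raise the SE of the duration-by-treatment interaction by only 1–3%. Subgroup size is the real limit: with half the patients acute, the SE of a contrast among acute patients is 4.187 × √(2/30) = 1.08 points. Stratification would not change that.
- **Place of the remedy.** Covariates may be set out in an analysis plan that is not shown. The allocation method and the overlapping categories are, however, stated in the article itself, and stratification has to be settled before allocation.

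**Conclusion.** The point holds as a matter of efficiency. The plan identifies a likely prognostic factor, has to record it, and then uses it in neither allocation nor the stated main analysis. There is no bias and no threat to the 3.97-point design difference. For an assumed 2-point contrast, the gain from using the factor is about 1 to 6 percentage points of power (74% to 75–80%) if half the patients are acute and the recovery gap is 1 to 3 points. With no gap there is no gain. Bonferroni correction or dropout would lower these power figures before and after the change. The overlap at exactly three months is a small but definite wording error and needs correcting in any case.

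**What to change.** 1. In {20b}, make the duration categories mutually exclusive: under 3 months, and 3 months or more.
2. In {20a}, prespecify this two-level factor and time since stroke at entry as baseline covariates in the PSQI and NIHSS models.
3. For any allocation still to be made, change {16a} and {16b} to two envelope series, one per duration category, each blocked over the four arms. Recruitment was due to run from April 2020 to about January 2022. If it is too far advanced, steps 1 and 2 can still be fixed before the analysis.

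The cost is a second envelope series and a few model terms. Duration is already needed for the planned subgroup, and the date of stroke should come with the medical history taken at the first visit ({18a}). The entry criteria need no change.

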#### Exclusion criteria

Participants who meet the following criteria will be excluded from the trial:
Had insomnia before stroke;Insomnia by poor sleep conditions [26];Have diagnoses of other sleep disorders, such as narcolepsy, obstructive sleep apnoea syndrome, or restless legs syndrome;Have neurological or psychiatric diseases;Have severe diabetes; hypertension; severe liver, kidney, or thyroid dysfunction; and severe cardiac insufficiency;Are unable to read, understand, and complete the forms or use the rating scales;Have implants that could interfere with EA or a history of hypersensitivity to EA;Had received TCM in the previous 1 month;Had participated in other trials;Are taking sleep-affecting diet or medication; orAre pregnant or preparing for pregnancy.

### Who will take informed consent? {26a}

The principal investigator at Yichang Hospital of Traditional Chinese Medicine will conduct the informed consent process, who will screen the potential participants in accordance with the inclusion and exclusion criteria. Written informed consent will be provided by eligible patients at the time of recruitment.

### Additional consent provisions for collection and use of participant data and biological specimens {26b}

During the intervention period, patients will have the right to withdraw for whatever reason and at whatever time. Therefore, on the consent form, participants are asked if they agree to the use of their data when they choose to withdraw from the trial. Participants will also be asked for permission for the research team to share relevant data with people from the Medical College of China Three Gorges University or Yichang Hospital of Traditional Chinese Medicine. This trial does not involve collecting biological specimens that will be stored.

## Interventions

### Explanation for the choice of comparators {6b}

In this study, we will assess whether EA combined with SZRD is more beneficial for post-stroke insomnia than independent usage of the two treatments. Therefore, EA, SZRD, and sham EA were chosen as comparators in this trial.

### Intervention description {11a}

All manipulators with acupuncturist qualification certificates have independently performed clinical treatments for more than 2 years. The acupuncturists will engage in the clinical training before the intervention to ensure experience with the standard real and sham acupuncture operations and will not be replaced during the trial.

Disposable acupuncture needles (0.35 × 25 mm or 0.35 × 40 mm, JiaJian Medical Instrument Co., Ltd, Wuxi, China), sham acupuncture needles with blunt tips (0.30 × 25 mm), G6805-2A EA devices (Huayi Medical Instrument Co., Ltd, Shanghai, China), and SZRD granules (Tcmages Pharmaceutical Co., Ltd, Beijing, China) will be used in this trial. The acupuncturists will use 0.35 × 25 mm needles for acupoints GV20, GV24, and HT7 and 0.35 × 40 mm needles for acupoint SP6. The depth of needle insertion will be 10–25 mm for each acupoint. Participants will receive EA or sham EA treatment every other day for 4 weeks for a total of 14 sessions, and participants receiving SZRD treatment will take 3.4 g SZRD granules orally twice a day for 4 weeks. After the baseline assessment, it will take 12 weeks for a patient to complete the trial, including 4 weeks of treatment and 8 weeks of follow-up (the intervention process chart is shown in Fig. 2B). Before the manual operation, patients will be asked to wear eye masks and lie supine. Each session will last for 30 min. The temperature in the isolated treatment room will be 25 °C (the interventions for all groups are shown in Table 1).

**Fig. 2 Fig2:**
[figure not shown]
The manipulation of the real and sham acupuncture device and intervention process chart. **A** The manipulation of the real and sham acupuncture. **B** The intervention process chart

**Table 1 Tab1:** Intervention parameters of each group

Groups	Interventions			
	Acupoints	EA parameters	Chinese herbs	Treatment sessions
EA & SZRD group	Bilateral HT7, bilateral SP6, GV20, GV24	Continuous wave stimulation; frequency = 10 Hz; current ranges from 1 to 5 mA	Suanzaoren, Zhimu, Fuling, Chuanxiong, Gancao	4 weeks, EA performed every other day, total 14 sessions; SZRD granules orally taken twice a day
EA group	Bilateral HT7, bilateral SP6, GV20, GV24	Continuous wave stimulation; frequency = 10 Hz; current ranges from 1 to 5 mA	No herbs	4 weeks, EA performed every other day, total 14 sessions
SZRD group	No acupoints	No parameters	Suanzaoren, Zhimu, Fuling, Chuanxiong, Gancao	4 weeks, SZRD granules orally taken twice a day
Sham group	Bilateral HT7, bilateral SP6, GV20, GV24 (no need inserting)	Frequency = 0 Hz; current = 0 mA	No herbs	4 weeks, sham EA performed every other day, total 14 sessions

